## Abstract

**Background:**

Patients with acute leukemia experience a substantial symptom burden and are at risk of developing infections throughout the course of repeated cycles of intensive chemotherapy. Physical activity in recent years has been a strategy for rehabilitation in cancer patients to remedy disease and treatment related symptoms and side effects. To date, there are no clinical practice exercise guidelines for patients with acute leukemia undergoing induction and consolidation chemotherapy. A randomized controlled trial is needed to determine if patients with acute leukemia can benefit by a structured and supervised counseling and exercise program.

**Methods/design:**

This paper presents the study protocol: **P**atient **A**ctivation through **C**ounseling and **E**xercise – **A**cute **L**eukemia (PACE-AL) trial, a two center, randomized controlled trial of 70 patients with acute leukemia (35 patients/study arm) following induction chemotherapy in the outpatient setting. Eligible patients will be randomized to usual care or to the 12 week exercise and counseling program. The intervention includes 3 hours + 30 minutes per week of supervised and structured aerobic training (moderate to high intensity 70 - 80%) on an ergometer cycle, strength exercises using hand weights and relaxation exercise. Individual health counseling sessions include a self directed home walk program with a step counter. The primary endpoint is functional performance/exercise capacity (6 minute walk distance). The secondary endpoints are submaximal VO_2_ max test, sit to stand and bicep curl test, physical activity levels, patient reported outcomes (quality of life, anxiety and depression, symptom prevalence, intensity and interference). Evaluation of clinical outcomes will be explored including incidence of infection, hospitalization days, body mass index, time to recurrence and survival. Qualitative exploration of patients’ health behavior and experiences.

**Discussion:**

PACE-AL will provide evidence of the effect of exercise and health promotion counseling on functional and physical capacity, the symptom burden and quality of life in patients with acute leukemia during out patient management. The results will inform clinical practice exercise guidelines and rehabilitation programs for patients undergoing treatment for acute leukemia. Optimizing the treatment and care pathway may ease the transition for patients from illness to the resumption of everyday activities.

**Trial registration:**

ClinicalTrials.gov Identifier: NCT01404520.

## Background

Acute leukemia is a life threatening hematological malignancy, representing one percent of all cancers diagnosed annually in Denmark, which approximates to 200 new cases of acute myeloid leukemia (AML) and 50 acute lymphatic leukemia (ALL) cases in adults yearly (cancer.dk). The five-year international survival for AML is 40% for adult patients (<60 yrs) receiving curative intended treatment, and for ALL 50% (18–45 yr) and 10-30% (>45 yr) [1,2]. The WHO performance status score of patients with AML at the time of diagnosis has been shown to have prognostic importance [3]. The primary goal of treatment for acute leukemia is to rapidly achieve complete remission attained by the initial intensive chemotherapy regimen (induction), followed by repeated cycles of intensive chemotherapy (consolidation) and if indicated, an allogeneic stem cell transplantation. Each chemotherapy cycle is followed by severe neutropenia, thrombocytopenia and anemia, with an increased risk of serious infections, mainly septicemia and pneumonia [4]. Deterioration of nutritional status and quality of life (QOL) is reported after induction treatment [5]. Patients report a substantial symptom burden including lack of energy, shortness of breath, weakness, comprised physical functioning, difficulty sleeping, pain, nausea, emesis, diarrhea, weight loss, anxiety and distress [5-7]. Further, clinically significant depression can be precipitated or exacerbated by a diagnosis of acute leukemia [8]. Multiple symptoms have been found to have a deteriorating effect on QOL in patients with hematologic malignancy [9-11].

Over the past 15 years, patient safety aspects and prolonged hospitalization have been challenged by homecare interventions and outpatient management programs triggered by the prospect of improving QOL by reducing hospital admissions [12]. Implementation of outpatient programs for patients with acute leukemia have enabled patients to be discharged to their homes while receiving mandatory antibiotic prophylaxis during neutropenic phases [13,14]. For the patient, this requires frequent, lengthy, long term and supervised visits for treatment and follow-up care, ongoing transfusion support and close monitoring for complications including serious infections. Pharmacological strategies, as antibiotic prophylaxis, antiemetics etc. are frequently prescribed to improve tolerance to the planned chemotherapy treatment, and now physical activity in recent years has been used as a strategy for rehabilitation in cancer patients to remedy disease and treatment related symptoms and side effects. Evidence suggests that activation of cancer patients can result in healthy behaviors i.e. physical activity, and lead to better health-related outcomes and self care management [15,16]. In addition, tailored counseling sessions have been shown to improve functioning, clinical outcomes and reduce hospitalization [17]. Feasibility, safety and beneficial effects of low to high intensity exercise and psychosocial interventions have been found in cancer patients with the majority being breast cancer, and to a much lesser extent in colon, prostate, lung and hematological malignancies [18-21]. However, the complex clinical situation seen in acute leukemia has predominantly excluded patients from participating in exercise interventions. Furthermore, present clinical care practice does not incorporate health counseling and physical exercise during treatment for acute leukemia which leaves this particular patient group understudied and under recruited in existing exercise-based rehabilitation programs. In a recent review of exercise in hematological cancer survivors [22], only three small scale studies comprise patients with acute leukemia [23-25], and one pilot study with a mixed population of acute leukemia and lymphoma [26], all during hospitalization while undergoing the induction phase of chemotherapy treatment. These limited findings, indicate feasibility, safety and preliminary physiological and psychosocial benefits from exercise in patients during induction treatment for acute leukemia. In our recently published pilot study (n = 20), we intervened in the outpatient management setting by building a bridge between the hospital and daily life activities of patients with acute leukemia by addressing the challenges associated with maintaining muscle, cardiovascular and emotional and general health during chemotherapy treatment [9]. This 6 week supervised and structured exercise and health counseling intervention proved feasible, safe and well tolerated with physical, functional, psychosocial and symptom benefits in a small sample of patients with acute leukemia undergoing intensive chemotherapy. However, no recommendation for exercise can be issued specifically for acute leukemia patients undergoing induction and consolidation treatment during hospitalization and outpatient treatment and care [9,22].

This protocol paper presents our current randomized trial (PACE-AL) that aims to investigate the effect of a 12 week structured and supervised multimodal program of physical exercise and health counselling in patients with acute leukemia undergoing consolidation treatment during outpatient treatment and care. It is hypothesized that the intervention can minimize the loss of physical and functional capacity, reduce the symptom burden, improve psychosocial wellbeing and health related QOL. To our best knowledge, this is a first time study that examines a multimodal intervention of health counseling and exercise in patients with acute leukemia, initiated early in the treatment trajectory prior to consolidation treatment and conducted over a 12 week period. The long term effect of the intervention will be investigated at 6 and 12 month follow-up.

## Methods/design

### Participants and setting

This randomized controlled trial is a prospective, two group trial of a 12 week exercise and health counseling intervention in patients with newly diagnosed acute leukemia during the course of consolidation treatment in the outpatient clinic. 70 patients will be consecutively recruited and randomized by the research investigator and/or the nurse specialists from the Department of Hematology at two Copenhagen University hospitals: The University Hospital of Copenhagen, Rigshospitalet (RH) and Herlev Hospital (HH). Patients ≥ 18 years newly diagnosed with acute leukemia are eligible for the study upon completion of their initial induction chemotherapy with a documented complete remission (CR) status, able to read and understand Danish and can provide a signed informed written consent. The exclusion criteria are recent symptoms of cardiovascular, neurological or muscular disease, abnormal electrocardiogram and uncontrolled high blood pressure.

### Study and recruitment procedures

The study flow is presented in Figure 1. Potential participants will be identified and screened for eligibility by the research investigator and/or clinical nurse specialist by weekly reviews of patient admissions and their status through medical record review and consultation with the nursing and medical staff at the Departments of Hematology, RH and HH. If eligible, the patients will be approached once the initial induction chemotherapy treatment is completed and complete remission (CR) is achieved. The patients will be provided with verbal and written information regarding the study and subsequently asked if they would like to participate. Once written consent is obtained, the patients are immediately scheduled for their baseline tests, which include four physical/exercise tests and asked to complete patient reported outcome questionnaires (PRO). Baseline tests and assessments will be repeated at 6 weeks and at completion of the intervention period (12 weeks). Selected participants (purposive sampling strategy) will be interviewed at 12 weeks by the research investigator (n = 25). Further, PRO tests will be repeated at 6 and 12 months. Three brief PRO pertaining to symptom assessment and physical activity levels will be repeated once weekly throughout the duration of the study period. To strengthen internal validity, the procedures for tests/assessments will be conducted under the same or similar conditions at all three test points at both hospitals (HH and RH). The study personnel and blinded outcome assessors will conduct tests during the morning hours (between 9 am-12 noon), utilize the same test equipment and conduct the tests/assessments in a specific order.

**Figure 1 F1:**
[figure not shown]
CONSORT diagram of patient recruitment and flow.

### Randomization and group allocation

After baseline testing, patients will be randomized to one of two trial arms (intervention or control) using the computerized Clinical Trial Management System (CITMAS/HITMAS) [27] and stratified for age (<45 and >45 years), gender, and treatment facility (RH and HH). This is to ensure that the randomized groups are similar at baseline. A block design with allocation weight of 1:1 will be used to generate treatment allocation. Randomized patients will remain in the same group for the entire duration of the intervention.

### Blinding

Blinding the participants or the investigators to allocation group will not be possible, however the outcome assessors and the trials statistician will be blinded to the participants study allocation. The trials statistician will have access to unblinded data, but will prepare results without knowledge of allocation to randomization coding.

### Trial arm 1 (intervention protocol and general considerations)

The intervention program - *exercise and counseling* (Tables 1 and 2) was designed using principles for exercise suggested by the American College of Sports Medicine (ACSM) [28] and a literature review on physical activity and hematological cancer survivorship [22]. The counseling sessions and the daily guidance and motivation are theoretically based on the social cognitive model of health promotion [29], theory of planned behaviour [30] and motivational interviewing (MI) methods and principles [31-34]. The intervention is a supervised hospital-based program that takes place at designated training locations at two hematology out-patient departments (RH,HH). Each session is designed to last 1hour ±10 min., 3 days weekly during the patients out-patient visit between 10 am and 12 noon beginning the first day of ambulatory care and carried out for 12 weeks. Patients who are intermittently hospitalized due to infection or other complications during the study period will be offered the intervention in their hospital room and when possible, the patient will be asked to meet at the projects designated training areas. Consecutive inclusion will enable training in small groups between 2 and 4 participants.

**Table 1 T1:** **The intervention program - *****exercise and health promotion counseling***

**PHYSICAL ACTIVITY**			**COUNSELING**	
**Physical Training**	**Relaxation Training**	**Diet**	**Guidance and motivation**	**Health counseling**
*Supervised (out-patient facility at hospital)*				
Stationary cycling	Relaxation and breathing exercise with guidance and music	Protein/carbohydrate supplement 30 min. after training	Instruction and guidance in exercising, usage of step counter and walking program, short and long term motivation and symptom management	Focus:
Moderate to very hard intensity				1) Screening
				2) Health behavior
75-80% HR max	Low intensity	e.g. chocolate milk, shake, nuts, protein bar		2) Handling of symptoms
Interval training	RPE 6-9			3) Social/employment
RPE 15-17	MET 2.5			
MET 5.5 - 8		Protein: 16-19 g.		GOAL SETTING
		Carbohyd: 1400-1900 kj.		
Dynamic and resistance training			Individual	Individual
Moderate to hard				
2 sets, 12 reps				
RPE 14-16				
MET 5.5				
3 days/week				3 sessions 30-60 min.
*Not supervised (home, outdoors, hospital corridor etc.)*				
Walk program with step counter				
Daily and individual				

**Table 2 T2:** **The weekly intervention program - *****exercise and health promotion counseling***

**WEEKLY PROGRAM 12 wks., 3 days/wk., 3-4 hours/wk. and daily walking**				
**Monday**	**Tuesday**	**Wednesday**	**Thursday**	**Friday**
Training program incl. relaxation (1 hr.)		Training program incl. relaxation (1 hr.)		Training program incl. relaxation (1 hr.)
Protein snack		Protein snack		Protein snack
Guidance and motivation		Guidance and motivation		Guidance and motivation
step counter		step counter		step counter
**Week 1**	**Week 2 - 11**			**Week 12**
Walk program with step counter	Walk program with step counter			Walk program with step counter
Establish habitual level	Maintenance or progression			Maintenance or progression
**Week 6**				
(1) Health counseling	(2) Health counseling			(3) Health counseling
(30-60 min)	(30-60 min)			(30-60 min)

#### ***Intervention: pre-screening and safety precautions***

The research investigator and/or the study’s clinical nurse specialists and physiotherapists will pre-screen the patients and supervise all sessions. If one or more of the following criteria are present prior to the intervention, the session will be either postponed or modified on that specific day; diastolic blood pressure < 45 or > 95 mmHg, pulse at rest > 100/min, signs of infection (temp > 38°C); respiration frequency at rest > 20/min and signs of bleeding (petechiae, nose bleeds, bruises). The units’ transfusion policy is for thrombocytopenia, platelets < 15 × 10^9^/l and for anemia, hemoglobin < 7.5 - 9 g/dl. The patients will be continuously monitored with a digital heart rate monitor (Polar Model) and observed for adverse reactions/events (see Monitoring Adverse Events).

The supervised *exercise* component of the intervention comprises *stationary cycling*, and will be initiated for a period of 20-25 min for each session. A minimum of six work intervals are integrated to enable cardiovascular effect while ensuring safety and therefore aims to reach but not exceed 80% of the maximal heart rate calculated by ACSM formula (206.9 - (0.67 × age) + 75/80%) [35]. The subjective intensity of effort is evaluated by the Borg Rate of Perceived Exertion scale (RPE), a visual analogue scale ranging from 6 (light effort) to 20 (maximal exertion) [36]. Intensity effort will strive to be between 15-17 (hard to very hard). The metabolic equivalent intensity level (METS) is calculated for each physical activity component [37]. The main goal of aerobic progression is to gradually increase exercise intensity and duration. Six *dynamic and resistance exercises* using free hand weights will be carried out including bicep curl, shoulder press, squat, lunge, push-ups, and one core exercise for abdominal and back muscles. Exercises will be performed in 2 sets of 12 repetitions, and hand weights will be adjusted to enable 2 sets and up to 12 repetitions. Progression aims to increase weight. The exercises will be followed by *relaxation training* while lying supine (or sitting) on a mat following live instruction to music [38-40]. At completion of each training session, the patients will consume a single or combined protein/carbohydrate supplement (16-19 g. protein and 1600–2000 kj carbohydrate) within 30 minutes of exercise to speed recovery by repairing and rebuilding muscle tissue [41,42]. Training sessions will be accompanied by guidance and motivation by the research physiotherapists and clinical nurse specialists with special focus on topics related to the exercise program, short and long term motivation and symptom management [29-34].

*Counseling* will be conducted three times for 30-60 min. at baseline, six and twelve weeks. Health promotion counseling sessions are schematized and carried out by the research investigator and/or clinical nurse specialists through a circular process of pre-contemplation, contemplation, preparation, action and maintenance [43]. The main principle of health counseling is to create a partnership with the patient to improve adherence to the intervention during the study period and to motivate towards positive health behavior, including maintaining or increasing physical activity during and beyond the supervised exercise sessions, and also after completion of the program. MI is a behavioral change strategy that assumes the patient possesses inherent resources and motivation that may be enhanced through the patient’s own expression of goals [29-34]. Each counseling session is therefore goal oriented and offers guidance in aspects of managing treatment-related symptoms, including symptoms of stress and anxiety, and issues related to diet, smoking cessation, alcohol consumption, sleep, social and daily life function and physical activity.

At the start of the program, the participants will receive a step counter (Omron Walking Style Pro) with the motivational purpose of physical and behavioral awareness and activation [44]. The patients will be fitted with the step counter by the study physiotherapists and instructed to wear the step counter during waking hours. Results from the step counter will be electronically transferred to a laptop computer once a week for the purpose of reviewing with each patient the number of daily total steps and aerobic steps achieved during the previous week, which will result in the patient expressing physical activity and walking goals for the following week.

### Trial arm 2 (control group)

*The control group receives* standard care and treatment that does not include supervised physical activity and/or health promotion counseling at the departments. Patients in both the intervention and control groups will receive usual care and treatment, and are not restricted from participating in other physical activity during the study period.

### Study endpoints and assessments

Outcome measures will be assessed at three time points, baseline, six and twelve weeks with a 6 and 12 month follow up. Table 3 outlines the study assessment schedule. Demographic, performance status (WHO) and medical data will be collected by journal review and questionnaire. Assessments will be carried out between 9:00 am and 12:00 noon by the project outcome assessors at their respective hospitals. Patients will be instructed on proper technique for the tests, and will be advised to stop if they experience pain or extreme discomfort, nausea, or dizziness. During the test sessions, the patients will be continuously monitored with a digital heart rate monitor (Polar Model) and observed for adverse reactions/events (see Monitoring Adverse Events).

**Table 3 T3:** Study assessment schedule

**Data Assessment**	**Screening**	**Day -2**	**Day 0**	**Day 1**	**6 weeks**	**12 weeks**	**6 months**	**12 months**
		**Baseline-test**			**Mid-test**	**Post-test**	**Follow-up**	**Follow-up**
*Recruitment*								
Chart review	x							
Patient approached	x							
Informed consent	x							
*Outcome Assessments*								
6MWD		x			x	x		
Aastrand-Rhyming test		x			x	x		
Sit to stand test		x			x	x		
Biceps arm curl		x			x	x		
Patient-reported outcomes		x			x	x	x	x
Medical chart review		x				x	x	x
*Weekly assessments*								
Step counter		x			x	x		
MDASI		x			x	x	x	x
BFI		x			x	x	x	x
PA Level		x			x	x	x	x
Randomization			x					
Intervention initiation				x				
Qualitative Interview						x		

**6MWD**, 6 minute walk distance; **MDASI**, M.D. Anderson Symptom Inventory; **BFI**, Brief Fatigue Inventory; **PA Level**, Physical Activity Level.

#### ***Primary endpoint***

*Functional performance/exercise capacity*: 6 minute walk distance (6MWD) which measures the sub maximal level of functional and exercise capacity and will be carried out in accordance with the American Thoracic Society (ATS) guidelines [45]. The ATS Pulmonary Function Standards Committee developed guidelines for the 6MWD in clinical settings [46]. The 6MWD was chosen because it is easy to administer in the outpatient setting, well tolerated by patients with acute leukemia, and reflects activities of daily living [47].

#### ***Secondary endpoints***

*Aerobic capacity.* A single stage 6 min submaximal exercise test; the Aastrand-Rhyming cycle ergometer test is used to predict VO_2_ max values [48]. The test is based on the linear relationship between VO_2_ and heart rate. The patients pulse will be continually monitored using a wireless heart rate transmitter. Resistance (Watt) is increased to elicit a steady-state heart rate between 125 and 170 beats/min at a speed between 60 and 65 r.p.m. If after 6 min the HR is above 125 beats/min and stable, not fluctuating more than 5 beats/min, the test is terminated. VO_2_ max is determined using a nomogram with an age and body weight correction factor. VOs max is stated in ml/kg/min.

*Functional performance and muscle strength* comprises three endpoints: *(1)* Sit to stand test will be performed as a measure of strength and performance of the lower extremity muscles. The 30 second sit to stand was developed as an assessment tool to measure lower body strength [49]; (2) Biceps Arm Curl measures arm flexor strength, upper body strength and endurance [50]. The aim is to perform as many arm curls as possible in 30 seconds; and (3) Measurement of weekly steps and distance with the step counter: Omron Walking Style Pro [44].

*Clinical outcomes* (exploratory endpoints) will include andropometric characteristics *(*body mass index (wt(kg)/ht(m^2^)), WHO performance status, hospitalization (days), increased temperature (>38°) (days), elevated C-reactive protein (days), infections and complications (type and days), neutropenia and thrombocytopenia (days), transfusions (platelets and RBC) (number), time to relapse and survival.

*Patient reported outcomes (PRO)* in this study are standardized and validated questionnaires that measure physical, functional, emotional and social wellbeing, symptom prevalence, intensity including fatigue and interference in daily activities. The PRO’s will be administered and checked for completeness by the study investigator at baseline, 6 and 12 weeks, and 6 and 12 months; and coded according to the guidelines given in the questionnaires manuals: (1) The Functional Assessment of Cancer Therapy-Anemia scale (FACT-An) assesses cancer specific Health Related Quality of Life (HRQOL), the fatigue symptom subscale (An) of the FACT-An scale and the Trial Outcome Index (TOI) [51]. (2) The 36-Item Short Form Health Survey (SF-36) assesses general wellbeing using eight scales measuring different aspects of general health with two summary scales; physical and mental component scales [52]. (3) The European Organization for Research and Treatment of Cancer Quality of Life Questionnaire (C30 EORTC QLQ-C30) assesses Quality of Life (QOL) using a global health status scale, five functional scales (physical, role, emotional, cognitive and social functioning) and symptom scales (fatigue, nausea and vomiting, pain, dyspnea, insomnia, appetite loss, constipation, diarrhea) [53,54]. (4) The Hospital Anxiety and Depression Scale (HADS) assess psychological wellbeing and is designed to measure general anxiety and depression in patients with physical illness [55]. (5) The M.D. Anderson Symptom Inventory (MDASI) assesses the severity of 13 symptoms and their impact as evaluated by six interference items [56]. The MDASI will be additionally administered once a week prior to the last training session. (6) The Brief Fatigue Inventory (BFI) assesses fatigue levels and their impact as evaluated by interference items [57]. The BFI will also be administered once a week prior to the last training session.

*Physical activity, social network/relations, activation and ability, and employment (return to work)* will be assessed by the (7) Leisure time physical activity [58], (8) Physical activity level [59], (9) Multidimensional Scale of Perceived Social Support (MSPSS) [60], (10) Patient Activation Measure (PAM) [61], (11) Self Efficacy Scale (GSE) [62] and (12) Employment status and ability [63].

*A qualitative in-depth face-to-face semistructured interview* (n = 25) at 12 weeks carried out by the study investigator will explore the patients’ perspectives on physical activity and health, health behavior, and the experiences and challenges (including barriers) of returning to daily life regarding issues of health (well-being, vitality/fatigue, strength, symptom control) and disease (treatment and management, symptoms, complications), social (network, family) and employment. Further, we would like to clarify whether and how the intervention has contributed to the patients’ experiences of physical, emotional and social wellbeing and adaptation. Moreover, we aim to describe the symptom experience from the patients’ perspective, as well as explore the effect of the intervention on the symptom burden and symptom interference. A topic and question guide will be used to aid the focus of the interviews.

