### Statistical considerations

#### ***Sample size***

This randomized controlled trial will include 70 acute leukemia patients over a recruitment period of 34–36 months. Sample size calculation is based on the primary endpoint; the 6 min walk distance (6MWD) and the results from our pilot study (n = 20), where n = 17 completed the study (15% lost to followup). The pilot study baseline for 6MWD was 450 m and the average change was 56.3 m effect (SD = 69.2). Assuming that there is no change in the control group, an inclusion of 70 patients (35 intervention, 35 control) will yield more than 90% power (risk of type 2 error set at 0.10) to detect a difference of this magnitude between groups using a significance level of 0.05 (risk of type 1 error set at 0.05). Should 20% be lost to followup (n = 56), the power will still be larger than 80%.

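### Chart review stops at each patient's month 12 while recruitment takes 34–36 months, so later relapses and deaths of early recruits fall outside the scheduled data for two exploratory endpoints

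*Protocol article*

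**What the plan says.** In the Protocol article, Secondary endpoints, the paragraph on clinical outcomes ends with "time to relapse and survival" and labels the whole group exploratory. The Abstract gives the same two outcomes the same status.

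Under Study endpoints and assessments, "medical data will be collected by journal review and questionnaire", and the timing is: "Outcome measures will be assessed at three time points, baseline, six and twelve weeks with a 6 and 12 month follow up". In Table 3 the row "Medical chart review" is marked at baseline, 12 weeks, 6 months and 12 months, with nothing after that. The last paragraph of the Background gives the same 6- and 12-month horizon for long-term effects.

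Under Sample size: "This randomized controlled trial will include 70 acute leukemia patients over a recruitment period of 34–36 months". The only event rates are in the Background. They start with "The five-year international survival for AML is 40% for adult patients" (those under 60 on curative treatment), followed by 50% for ALL at 18–45 years and 10–30% for ALL above 45. No relapse rate, closing date or censoring date is stated.

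**The concern.** A fixed 12-month window suits the questionnaires, which need the patient's participation. Relapse and vital status are different: they are read from records, and the trial as a whole stays open about three years longer than the window of its first patient. On the schedule as written, an early recruit who relapses in month 14 is not captured as an event, although this could be known well before the last patient finishes.

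At stake is the precision of the only listed outcomes that bear directly on disease control, in a population that the Background calls understudied in exercise research. With 70 patients every event counts. An analysis plan cannot recover events that the schedule never collected.

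**Working it through.** **The plan's own figure.** The article gives no event count or power for relapse or survival; its power statement concerns the 6-minute walk distance. That statement reproduces. With 35 per arm, 56.3 / (69.2 × √(2/35)) = 3.40, and 3.40 − 1.96 = 1.44, so power is 92.6% (91.8% with the t distribution). With 28 per arm it is 86.1% (84.8%). Nothing below touches it.

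**Inputs from the article.** N = 70, 1:1 allocation; recruitment R = 34 to 36 months; last chart review at 12 months; five-year survival S5 = 40% (AML under 60), 50% and 10–30% (ALL by age).

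**Assumptions.** Uniform accrual. A common close when the last patient reaches 12 months. The five-year survival figures apply from trial entry.

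**Step 1: follow-up time, no hazard model needed.** Potential follow-up at the common close runs from 12 to 12 + R months, with mean 12 + R/2, that is 29 to 30 months. The unused share is 1 − 12/29 = 59% to 1 − 12/30 = 60% (70 person-years against 169 to 175, counted before deaths).

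**Step 2: deaths, constant hazard.** At S5 = 40%, h = −ln(0.40)/5 = 0.183 per year.
- By 12 months: 70 × (1 − e^(−h)) = 11.7.
- By the common close, with R in years: 70 × (1 − [e^(−h) − e^(−h(1+R))]/(hR)) = 24.5 (R = 34 months) to 25.2 (36 months).
- Share left out: 1 − 11.7/24.5 = 52% to 1 − 11.7/25.2 = 53% (from unrounded counts).

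| Five-year survival | Deaths by 12 months | Deaths by common close | Left out |
|---|---|---|---|
| 50% | 9.1 | 19.6–20.1 | 54–55% |
| 40% | 11.7 | 24.5–25.2 | 52–53% |
| 30% | 15.0 | 30.1–30.8 | 50–51% |
| 10% | 25.8 | 45.3–46.1 | 43–44% |

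**Step 3: deaths, falling hazard.** Weibull survival S(t) = exp(−λt^k), with t in months and λ set so that S(60) = S5.

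| Shape k, at S5 = 40% | Deaths by 12 months | Deaths by common close | Left out |
|---|---|---|---|
| 0.8 | 15.6 | 27.4–28.0 | 43–44% |
| 0.7 | 18.0 | 29.0–29.5 | 38–39% |
| 0.5 | 23.5 | 32.4–32.7 | 27–28% |

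Over all the survival figures and shapes 0.8 to 0.5 the loss is 18–46%. Curves with a long-term surviving fraction (25–45%, for S5 of 30–50%) give 36–43%.

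**Step 4: precision.** SE(log HR) ≈ 2/√events. Under the constant hazard at 40%:
- 12 months: 2/√11.7 = 0.58, 95% limits a factor e^(1.96 × 0.58) ≈ 3.1 either side.
- Common close: 2/√25 = 0.40, factor e^(1.96 × 0.40) ≈ 2.2.
- Power for a hazard ratio of 0.5: 22% against 41%.

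The SE falls by about 31%. With k = 0.5 it goes from 2/√23.5 = 0.41 to 2/√32.4 = 0.35, a fall of about 15%.

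**Step 5: relapse.** The article gives no relapse rate, so there is nothing to put into these formulas. If relapse tends to come earlier than death, the share missed would be smaller than for deaths.

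**The case against.** The strongest reply is that the cut-off is inferred. The article states no censoring rule for these endpoints, Table 3 is a per-patient schedule whose chart-review row also serves hospital days, infections and transfusions, and a data cut-off may stand in the full protocol or SAP. That is a fair caution, and a missing censoring rule is not the point here. What remains is a stated schedule: the table, the text on assessments and the Background agree on 12 months, and none mentions a later look. If a later review is planned elsewhere, one line answers the point.

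Second, a fixed horizon is a legitimate choice. The programme lasts 12 weeks, controls may exercise, and any effect may be diluted in events years later, so more events need not bring proportionally more information. This stands, and is the reason to keep the 12-month result beside the longer one.

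Third, the added events settle nothing: limits of a factor of 2.2 are still wide. This also stands, and limits the point to a minor improvement.

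A reader might go further and infer that half of all relapses and deaths are thrown away, for no saving, in patients observed at the same two hospitals for nearly four years. The article does not support that. Half needs a constant hazard and, for the 40% case, a figure for AML under 60 applied to patients with AML or ALL, with no upper age limit, already in complete remission. Relapse has no rate at all. No cost of chart review is given, and the Discussion says only that patients are typically outpatients for months after induction, not that they stay at these hospitals for years.

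**Conclusion.** The point holds as a minor design improvement, not as an error. Followed as written, the schedule leaves unread the relapses and deaths of early recruits after month 12. About 59–60% of potential follow-up time to a common close is unused, given uniform accrual. For deaths the loss is about a fifth to a half: around 52% under a constant hazard at 40% five-year survival, and 27–44% under the front-loaded hazards tried at the same survival. For relapse it is unknown.

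The gain in precision is correspondingly about 31% in the SE at best guess under constant hazard and about half that under the steepest early hazard. All the death counts borrow general survival figures for patients already in remission. Conclusions on the primary endpoint, the sample size and the main analysis do not change.

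**What to change.** Add one column or line to Table 3: a chart review of relapse and vital status for all randomised patients on the date when the last patient reaches 12 months. Analyse both endpoints as time-to-event data, censored at that date or at the last available record if that is earlier. Report the 12-month result alongside, and keep both endpoints labelled exploratory.

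The cost is one record look-up for up to 70 patients and a check that consent and the data permission cover it. It needs no new patient, no extra visit and no delay, because the last scheduled follow-up falls on the same date.
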